## Abstract

**Introduction:**

People who are immunocompromised have a poor biological response to vaccinations. This study aims to determine in patients with chronic lymphocytic leukaemia (CLL) if a 3-week pause in Bruton tyrosine kinase inhibitor therapy (BTKi) starting 1 week before delivery of SARS-CoV-2 vaccine booster, improves vaccine immune response when compared with continuation of BTKi.

**Methods and analysis:**

An open-label, randomised controlled superiority trial will be conducted in haematology clinics in approximately 10 UK National Health Service (NHS) hospitals. The sample size is 120, randomised 1:1 to intervention and usual care arms. The primary outcome is anti-spike-receptor binding domain (RBD) antibody level at 3 weeks post-SARS-CoV-2 booster vaccination. Secondary outcomes are RBD antibody levels at 12 weeks postbooster vaccination, participant global assessments of disease activity, blood films, full blood count and lactate dehydrogenase levels, impact on quality of life, self-reported adherence with request to temporarily pause or continue BTKi, T cell response against spike protein and relative neutralising antibody titre against SARS-CoV-2 viral variants. Additionally, there will be an investigation of any effects in those given influenza vaccination contemporaneously versus COVID-19 alone.

The primary analysis will be performed on the as randomised groups (‘intention to treat’). The difference between the study arms in anti-spike-RBD antibody level will be estimated using a mixed effects regression model, allowing for repeated measures clustered within participants. The model will be adjusted for randomisation factor (first line or subsequent line of therapy), and prior infection status obtained from prerandomisation antinucleocapsid antibodies as fixed effects.

**Ethics and dissemination:**

This study has been approved by Leeds East Research Ethics Committee and Health Research Authority (REC Reference:22/YH/0226, IRAS ID: 319057). Dissemination will be via peer-review publications, newsletters and conferences. Results will be communicated to participants, the CLL patient and clinical communities and health policy-makers.

**Trial registration number:**

ISRCTN14197181.

STRENGTHS AND LIMITATIONS OF THIS STUDYIt is adequately powered to detect modest differences in anti-spike receptor binding domain (RBD) antibody titres that have been deemed clinically important, alongside what impact there is on the functional quality of responses observed. Therefore, it will provide information about both the benefits and risks of temporarily pausing treatment.This is an open-label study so both participants and researchers will be unblinded to group allocation, however, the primary and key secondary outcome measures are laboratory assessed by staff blinded to group allocation.The different vaccine types available in the latest vaccination programme may impact the study results—the latest Sanofi vaccination does not contain ancestral SARS-CoV-2 spike protein which is the antigen used in the RBD spike assay on which the primary outcome is based.

## Introduction

Chronic lymphocytic leukaemia (CLL) is the most common adult leukaemia in many countries with 3800 new diagnoses each year in the UK.^1–3^ It is a chronic and currently incurable disease that demonstrates wide clinical heterogeneity.^4 5^ CLL occurs predominantly in older people and is rare below the age of 40 years. An estimated 31 900 people are living with CLL in the UK.^6–8^

People who are immunocompromised have a poor biological response to vaccinations.^9^ CLL is associated with underlying immune suppression. This can lead to considerable risk of infection with associated morbidity and mortality.^10^ Infection remains the cause of death for around 25% of patients with CLL.^11 12^ Most recently, people with CLL were shown to be susceptible to severe COVID-19 and have been prioritised for receiving SARS-CoV-2 vaccines.^13–17^ Unfortunately, vaccine responses in patients with CLL are impaired, particularly in those on current ‘targeted’ drugs (Bruton tyrosine kinase inhibitors (BTKi)) that act to inhibit B cell receptor function. This class of drug is highly effective in suppressing the CLL tumour and is taken continuously in the long term.^18–22^ New approaches to improve immune protection in patients with CLL are needed.^23^ In this study, we seek to investigate if a pragmatic modification of CLL therapy could act to have an impact on vaccine induced immunity in this clinically vulnerable group.

We hypothesise that people taking BTKi specifically Ibrutinib or Acalabrutinib for their CLL at the time of vaccination against COVID-19 (±an influenza vaccination) will have an impaired immune response to the vaccine dose, and therefore, lower production of anti-spike-receptor binding domain (RBD) and neutralising antibodies. We propose that a 3-week pause in BTKi treatment will improve the vaccine-specific immune response, without significant worsening of the control of the underlying CLL, when compared with continuation of treatment as usual. The design and delivery of this study was based around another trial that assessed pausing the immune suppressant drug methotrexate around the time of COVID-19 vaccination in patients with inflammatory disorders.^24^ Pausing of CLL therapy is not uncommon and is recommended perioperatively due to the off-target effect of BTKi therapy on platelet function, which results in an increased bleeding risk.^25 26^ Individuals can then experience a disease flare (which can include enlargement of lymph nodes and/or “B symptoms”, such as fever, sweats and weight loss); most are mild with symptoms such as a fever, rash or mild pain, but some can experience raised lymphocyte counts, enlarged spleens, and pain and changes seen in their blood biochemical profiles.

Currently, no randomised trials have examined the impact of pausing BTKi therapy in patients with CLL for vaccine responsiveness. However, several observational studies have shown poorer responses in those taking BTKi and in addition, improvement in responses off therapy. In the CLL-VR study, following the second dose of vaccine, response rates were almost half in patients who took a BTKi compared with healthy controls.^27^ Greenberger *et al* studied responses to a third dose of COVID-19 vaccination in 25 patients with CLL, 13 of whom were treated with BTKi. Of these, 6/13 had an elevated anti-Spike response but 4 had stopped therapy and one was maintained on a low dose. In comparison, among those who continued therapy, five had a very weak response (<5.2 U/mL) and two had an intermediate response (<250 U/mL).^28^ These data suggest that both the proportion of responders and the strength of response increases in patients not taking BTKi therapy.

Thus, the main aim of this study is to assess whether a 3-week pause in BTKi treatment, 1 week before and 2 weeks after SARS-CoV-2 vaccine booster, improves the vaccine response in people with CLL, compared with continuing BTKi treatment as usual. Key secondary outcomes include any impact on quality of life (QoL) and disease activity.

### Objectives

Primary: Assess the effectiveness of a 3-week pause in BTKi, rather than continuing treatment as usual, on anti-spike-RBD antibody levels at 3 weeks post-SARS-CoV-2 booster vaccination.

Secondary and exploratory: Assess the effectiveness of a 3-week pause in BTKi treatment rather than continuing treatment as usual, on:

Anti-spike-RBD antibody levels at week 12 after booster vaccination.Neutralising antibody titres at baseline and week 3 after booster vaccination against Wuhan D614G and current variant of concern.Effect on T cell response to SARS-CoV-2 spike protein at 3 weeks postbooster vaccination.Responses to booster vaccination at 3 and 12 weeks after vaccination when influenza vaccination was given at the same time.Biochemical disease activity at weeks 3 and 12 postbooster vaccination.Disease activity changes and their tolerability as reported by participants during the 12 weeks postbooster vaccination.QoL at weeks 3 and 12 after booster vaccination.Self-reported adherence to the allocation.

## Methods

### Study design

A two-arm parallel group, multicentre, superiority randomised controlled trial, with 1:1 randomisation. This study will be conducted in approximately 10 NHS hospitals in England and Wales. These will be a mix of district general and university hospitals. Figure 1 provides an overview of the study.

**Figure 1 F1:**
[figure not shown]
Participant flow in the IMPROVE study. CTU, Clinical Trial Unit; SMS, Short Message Service; BTKi, Bruton tyrosine kinase inhibitor; OCTRU, Oxford Clinical Trials Research Unit.

### Recruitment

Participants will be recruited from haematology clinics. Searching of clinic records/hospital/pharmacy databases by the usual care team and identification during routine clinic visits will be the main methods of identification of potentially eligible patients. Social media and promotion of the study by national patient charities, will enable people taking BTKi for their CLL to directly approach their local study teams (or the study centre) to find out more about the study. People identified in the database reviews will be sent a study introductory letter, a participant information leaflet, and a reply slip to return if they are interested in taking part. For those identified directly in clinics, they will be offered the participant information leaflet and the study introductory letter if appropriate.

### Eligibility criteria

#### Inclusion criteria

Age ≥18 years.Confirmed diagnosis of CLL.Taking oral BTKi therapy (Acalabrutinib or Ibrutinib) for at least 12 months.Has achieved complete remission (including CR with incomplete marrow recovery), partial remission (PR) (including nodular PR or PR with lymphocytosis) or stable disease by the International Workshop on chronic lymphocytic leukaemia response criteria.^29^Considered able to pause BTKi therapy for 3 weeks without the risk of substantial increase in disease activity.Anticipated to take BTKi over the next 4 months.Willing to accept either study arm allocation.Able to give informed consent.Eligible for a planned booster vaccination for COVID-19.

#### Exclusion criteria

Insufficient time for applying the intervention prior to the planned COVID-19 booster vaccination.Diagnosed with alternative conditions requiring treatment with BTKi.Treated with anti-CD20 antibody therapy in the last 18 months or planning to start it.Concurrent immune suppressive treatments in the last 3 months specifically: methotrexate, ciclosporin, BCL-2 inhibitors, azathioprine, mycophenolate, prednisolone and biological agents.Any contraindications to COVID-19 vaccination.Richter’s transformation requiring active therapy.Radiotherapy or cancer chemotherapy in last 6 months.Active solid organ cancer (people with skin cancer or those cured of solid organ cancer are eligible).Receiving or has received in the past 6 months immunoglobulin replacement therapy.Receiving or has received in the past 6 months monoclonal antibody therapy against COVID-19 spike protein.

### Randomisation

This will be performed using a centralised validated computer randomisation programme through a secure (encrypted) web-based service, provided by the Oxford Clinical Trials Research Unit (OCTRU). Eligible participants will be randomised when they receive a date for their SARS-CoV-2 booster vaccination. The randomisation system will stratify on whether the participant is on their first line or subsequent line of therapy for CLL to ensure balanced allocation across treatment groups. It will use a 1:1 ratio to allocate to either continuing taking BTKi as usual or to have a 3-week pause (1 week before and 2 weeks after their booster vaccination against COVID-19).

Randomisation will be stratified on the line of CLL therapy being used as it has already been shown that the magnitude of immune response differs depending on the number of lines of therapy.^27^ We have chosen not to stratify on past COVID-19 infection even though it is a strong modifier of serological response to SARS-CoV-2 vaccines as it is difficult to ascertain this reliably from participant self-report. We are also not stratifying on the first vaccine platform received (eg, adenovirus vector or mRNA) as we have previously shown that there is no difference in the magnitude of antibody response by vaccine platform in patients with CLL,^27^ nor on which BTKi therapy the participant is currently taking. However, we will obtain past infection status using anti-nucleocapsid antibodies and use this in the statistical analysis. Due to the nature of the intervention, the participants and the clinical team will not be blind to the allocated arm of the study. However, those analysing the study samples will be blinded to the participants’ allocation. Trial statisticians will not be blinded.

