### Treatment arms

The SARS-CoV-2 booster vaccination received while participating in the IMPROVE study will be delivered by the UK’s national vaccination programme.^30^ If another vaccine such as influenza is given at the same time, these data will be recorded.

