#### Experimental arm

To suspend BTKi therapy for 1 week before and 2 weeks immediately after receiving the booster vaccination against COVID-19.

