### Outcomes

#### Primary outcome

SARS-CoV-2 spike RBD-specific antibody titre at 3 weeks postbooster vaccination (PBV).

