#### Safety outcomes

Serious adverse events (SAEs) that are related to study intervention (recorded from booster vaccination to 12 weeks PBV).

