### Three weeks PBV (±4 days)

Information about any COVID-19 positive testing, a participant’s global assessment of disease activity will be collected, the latter using the same questions asked at the baseline visit asking for the last 7 days and also in the 3-week period since their booster. QoL will be assessed using EORTC-QLQ-CLL17. These data will be generally collected using a link to the study’s online REDCap database sent in a text message, or by email if participant prefers not to use a mobile phone for this purpose. If a participant prefers not to receive this survey link by email or text, this information will be collected by postal questionnaires or at the study visit.

The local research team will collect data at this visit about a participants COVID-19 vaccination history including the most recent COVID-19 vaccination received, details of any other vaccinations coadministered and adherence to the study intervention. In addition, details of any monoclonal antibody treatment will be collected and bloods taken and blood tests undertaken as at baseline. Details of any SAEs will also be recorded.

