### Sample size and justification

A total of 120 participants will be randomised. The sample size estimates were based on the anti-spike-RBD response after vaccination dose from a small observational study of patients with CLL who were either taking or not taking BTKi.^27^ This suggested a large suppressive effect of BTKi (effect size of 0.9SD). However, anti-spike RBD response related to booster vaccination in CLL patients suggests a smaller though still large effect is more plausible (circa 0.7 SD). Conservatively, we have based the sample size calculation on an effect size of 0.65SD (detecting at least a 0.97 unit (log10 scale) higher antibody response in the BTKi suspension group with 90% statistical power at two-sided 5% significance level which requires data from 102 participants. This leads to 120 participants after allowing for 15% missing data. This calculation was performed using the Stata V.15.1 ‘power twomeans’ command.

Statistical analysis: Full details will be presented in a separate statistical analysis plan which will be drafted and finalised and aimed to be published prior to the final analysis data lock and will receive review and input from the trial steering committee (TSC) and data monitoring committee. The principal analysis will be performed on the as randomised (‘intention-to-treat’) population, analysing participants with available outcome data in their randomised groups, regardless of adherence. The study will be reported in line with Consolidated Standards of Reporting Trials guidelines.^35^

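### SAE recording and the 3-week disease-activity recall start at the booster, so the first week of the pause, and anyone never boosted, falls outside the stated safety window

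*Protocol article*

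**What the plan says.** Participants enter the comparison before the booster: "Eligible participants will be randomised when they receive a date for their SARS-CoV-2 booster vaccination" (Protocol article, Randomisation). The experimental arm is "To suspend BTKi therapy for 1 week before and 2 weeks immediately after receiving the booster vaccination against COVID-19" (Experimental arm). The booster itself is "delivered by the UK’s national vaccination programme" (Treatment arms), so the trial does not control whether or when it is given.

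The safety outcome is SAEs related to the intervention, "recorded from booster vaccination to 12 weeks PBV" (Safety outcomes). At the 3-week visit, participants rate disease activity over the last 7 days and over the three weeks since the booster. The Objectives likewise frame participant-reported disease activity as change over the 12 weeks after the booster. Table 1 places safety and disease-activity follow-up at 3 and 12 weeks after vaccination only; the columns for one week before vaccination and for vaccination itself hold reminders and an optional blood sample.

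The statistical analysis text under Sample size and justification uses a different origin. It compares the proportion of participants with at least one SAE and reports the timing of events from randomisation.

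**The concern.** Exposure to the intervention starts a week before the clock that records its harms. The Introduction says that stopping BTKi can bring a disease flare, and the Discussion says that flare data are collected so that risk can be weighed against benefit. A serious event in the pre-booster week is therefore exactly what the safety outcome should capture, yet its definition leaves that week out.

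The omission covers the same calendar period in both arms, but its effect does not fall equally. Controls have changed nothing in that week, while the pause arm has stopped treatment. The safety outcome is also limited to intervention-related events, so what is lost would come almost entirely from the pause arm. In an open-label trial meant to inform treatment guidance, the error runs towards making the pause look safer.

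A participant who pauses and is then not boosted is the extreme case: treatment was stopped because of the allocation, and the recording window never opens.

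**Working it through.** **Time line, with day 0 the actual booster**

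| Item | Start | End | Source |
|---|---|---|---|
| Pause | day −7 | day +14 | Experimental arm |
| SAE recording | day 0 | day +84 | Safety outcomes |
| 3-week visit | day +17 | day +25 | 21 ± 4 days |
| Origin for SAE timing | randomisation | – | Statistical analysis text |

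**SAE window against the pause.** The pause lasts 7 + 14 = 21 days. The window covers days 0 to 14 of it, which is 14/21 = 67%, and leaves out 7/21 = 33%. From the start of the pause to week 12 there are 7 + 84 = 91 days, of which 7/91 = 7.7% are unrecorded. The loss is small as a share of follow-up, but it is the first third of the exposure.

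**Recall at the 3-week visit.** The last-7-days question reaches back to day 17 − 7 = 10 at the earliest visit and day 25 − 7 = 18 at the latest. The other question reaches back to the booster, day 0. Neither goes before day 0. The baseline assessment precedes randomisation, so it does not cover the pre-booster week either.

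**Fit with the analysis text.** Assume that randomisation leaves room for the full pre-booster week, so that it falls on day −7 or earlier. A display of SAE timing from randomisation must then be empty for at least its first 7 days, because of the recording rule and not because nothing happened.

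**Never boosted.** With no booster there is no day 0, so the interval from booster to 12 weeks after it does not exist.

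**Scale per event.** With 120 randomised 1:1, each arm has 60. If all 60 stay in the denominator, each pause-arm participant whose only related SAE falls in the unrecorded period lowers that arm's proportion by 1/60 = 1.7 percentage points. The documents give no event rate for that week and no non-booster rate, so this cannot be turned into an expected bias.

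**Power is not the issue.** The plan's sample size reproduces. A two-sample t-test with effect 0.65 SD, two-sided 5% and 90% power needs 50.7, so 51 per arm or 102, and 102/0.85 = 120. If non-boosting falls within the 15% missing-data allowance, power stays at 90.2%. If an assumed further 5% or 10% were lost on top of it, 96.9 or 91.8 would be evaluable, with power 88.6% or 86.9%.

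**The case against.** The strongest reply is that this is a condensed article. The full protocol, the supplement, the SAP and the participant-flow figure are not shown, and any of them may start SAE reporting earlier or say what happens when a booster is cancelled. Site staff are also told to record details of any SAEs at the 3-week visit, with no start date given there, so an early event might be noted in practice. Eligibility is restricted to people considered able to pause without substantial risk, and the article describes most flares as mild, so serious events in that week may be few.

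The last point stands and bears on the size. The first two do not dispose of the concern: the Safety outcomes sentence is not a silence to be filled elsewhere but a stated start date, and it conflicts with another stated origin in the same article.

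A reader might go further and infer that unboosted participants lose all follow-up and leave both the intention-to-treat and the harm analyses. The documents do not support that:

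- The article gives no rule for the unboosted; their loss is an inference from how the visits are labelled.
- The restriction to "analysing participants with available outcome data in their randomised groups, regardless of adherence" describes the principal analysis. No boosted-only denominator is stated for SAEs, so such a participant might be counted with no recorded event.
- A baseline sample could keep the participant in the mixed model if baseline is a response, though without post-booster information.
- The plan allows for 15% missing data and will describe missing data by arm with reasons.
- A booster that is deferred and later given starts every clock as intended. Only a booster never given leaves the gap.

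**Conclusion.** The concern holds in a limited form. As written, the safety window and the 3-week recall omit the first of the three pause weeks for every pause-arm participant, the SAE window never opens for anyone not boosted, and the start date does not fit the reporting of SAE timing from randomisation. The likely direction is understatement of harm in the pause arm.

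This rests on the literal wording of the Safety outcomes section and on the pause starting a week before the booster. The size is unknown: the documents give neither the rate of serious events in the pre-booster week nor the share of participants not boosted, and any percentage bias quoted would be invented. The primary antibody comparison and the sample size are not called into question. The wording should be corrected, because the gap falls on one arm's risk and is cheap to close.

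**What to change.** - **Safety outcomes:** start SAE recording at randomisation in both arms and run it to 12 weeks after the booster. Reconcile this with the statistical analysis text, which already uses randomisation as the origin.
- **3-week visit:** extend the flare and disease-activity recall back to the start of the pause, and to the same calendar point in controls.
- **Never boosted only:** collect safety, disease-activity and QoL data at 3 and 12 weeks from the planned booster date, which is known at randomisation.
- **Booster postponed but given:** keep all visits timed from the actual booster. Using the planned date here would mistime the primary sample: with a 2-week postponement, the week-3 sample would be drawn 1 week after vaccination.
- **Analysis:** include all randomised participants in the SAE denominator, and report booster receipt and date by arm.

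The cost is a slightly longer recording window, one reworded recall question and a few extra contacts for people not boosted. The sample size and the primary analysis do not change.
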